### 2.3. Sample Size

Sample size estimation for the pilot trial was guided by the recommendations of Whitehead et al., [15] for pilot randomized trials. These recommendations indicate that pilot studies should recruit sufficient participants to provide preliminary estimates of effect size that can inform the sample size calculation for a subsequent definitive trial.

Based on these guidelines, approximately 15–25 participants per group are considered adequate for pilot trials investigating continuous outcomes with moderate effect sizes. Therefore, the present study aims to recruit approximately 72 participants in total, with 24 participants allocated to each study group (morning HIIT, evening HIIT, and control).

For the qualitative component, interview-based studies typically achieve data saturation with 9–17 participants [16]. Therefore, approximately 10–15 participants will be purposively selected for interviews. Additional interviews will be conducted if new themes continue to emerge during analysis.

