### 2.9. Outcome Measure

#### 2.9.1. Feasibility Outcomes

The primary outcomes of the study are feasibility indicators, including recruitment rate, retention rate, adherence rate and data missing rate. Recruitment will be considered successful if more than 70% of eligible students agree to participate. Retention will be considered acceptable if more than 80% of participants complete the intervention. Adherence will be defined as participation in more than 70% of the prescribed training sessions. To account for partial participation, adherence will also be calculated as the proportion of completed training sessions relative to the total number of prescribed sessions. Participants who attend some, but not all, scheduled sessions will therefore be categorized according to their overall attendance percentage. The overall missing data rate is expected to remain below 10% [23,24]. Feasibility thresholds were established based on recommendations for pilot and feasibility trials and commonly used progression criteria in feasibility research [25].

Safety-related outcomes will include the number, type, severity, and relatedness of adverse events occurring during the intervention period. Adverse events will include any undesirable physical or psychological symptoms occurring during or after the HIIT sessions, such as musculoskeletal pain, dizziness, excessive fatigue, nausea, shortness of breath beyond expected exertion, or injury. Events will be categorized as mild, moderate, or severe, and as unrelated, possibly related, or probably related to the intervention. These safety indicators will be used to evaluate whether the Chrono-HIIT programme can be delivered safely among college students with low prior physical activity levels.

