### 2.12. Statistical Analysis

All statistical analyses will be conducted using IBM SPSS Statistics version 27.0 (IBM Corp., Armonk, NY, USA). Descriptive statistics will be used to summarize participant characteristics, feasibility outcomes, and safety indicators. Continuous variables will be presented as means and standard deviations for normally distributed data, while medians and interquartile ranges will be reported for non-normally distributed data. Categorical variables will be presented as frequencies and percentages.

Prior to inferential analyses, the distribution of continuous variables will be assessed using the Shapiro–Wilk test and graphical inspection methods, including histograms and Q–Q plots. Homogeneity of variance and sphericity assumptions will also be evaluated where appropriate. Mauchly’s test of sphericity will be performed for repeated-measures analyses, and Greenhouse–Geisser corrections will be applied if the assumption of sphericity is violated.

As this study is designed as a feasibility pilot randomized controlled trial, analyses of intervention effects will be considered exploratory in nature. Therefore, greater emphasis will be placed on estimating effect sizes and confidence intervals rather than relying solely on statistical significance testing. Mixed designed ANOVA will be used to explore the effects of time (pre-intervention vs. post-intervention), group (morning HIIT, evening HIIT, and control), and time × group interactions on health-related physical fitness outcomes.

If substantial deviations from normality are observed, appropriate remedial approaches such as data transformation or robust statistical procedures will be considered. In addition, non-parametric analyses may be conducted as sensitivity analyses to evaluate the robustness of the findings.

Effect sizes will be calculated to provide preliminary estimates of intervention effects and to inform sample size estimation for future fully powered randomized controlled trials. Statistical significance will be set at *p* < 0.05. Where appropriate, intention-to-treat analyses will be performed to account for missing data and participant attrition.

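### Intention-to-treat is offered conditionally and as the cure for missing data, but the only named model is a pre/post mixed ANOVA that is complete-case by default

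*Protocol article*

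**What the plan says.** All of this is in the protocol article. Section 2.12 fixes the software ("All statistical analyses will be conducted using IBM SPSS Statistics version 27.0") and one model for the fitness outcomes: "Mixed designed ANOVA will be used to explore the effects of time (pre-intervention vs. post-intervention), group (morning HIIT, evening HIIT, and control"), together with their interaction. The same section adds that Mauchly's "test of sphericity will be performed for repeated-measures analyses", with a Greenhouse–Geisser correction if needed. That is the language of the classical repeated-measures routine, not of a likelihood-based mixed model.

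The section closes with: "Where appropriate, intention-to-treat analyses will be performed to account for missing data and participant attrition". The article does not say when this is appropriate, and it does not say how the ANOVA would accommodate a participant with no post-test.

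Two feasibility criteria in section 2.9.1 bear on the size of the problem. The first is "Retention will be considered acceptable if more than 80% of participants complete the intervention". The second is "The overall missing data rate is expected to remain below 10" per cent. Section 2.3 "aims to recruit approximately 72 participants in total, with 24 participants allocated to each study group". Section 2.12 calls the effect analyses exploratory, but it puts the emphasis on effect sizes and intervals. Sections 2.9.2 and 2.12 both say that the effect sizes will inform the sample size of a later definitive trial.

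**The concern.** Intention-to-treat settles who is analysed and in which arm. It does not supply or model an outcome that was never measured, so it cannot by itself account for attrition. That work falls to the model, and the model named here uses only people with both visits. The stated aim and the stated method therefore do not meet.

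The qualifier 'where appropriate' adds to this. With no criterion attached, the analysis set can be settled after attrition is known, and section 2.1 blinds the data analysts only as far as feasible.

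At stake are the estimates that the trial is meant to hand on. An eight-week high-intensity programme may lose students unevenly across the morning, evening and control arms. If the reason for leaving is related to baseline fitness or to response, a complete-case contrast is biased, and the next trial would be planned on it.

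**Working it through.** **1. The plan's own figure.** 3 arms × 24 = 72, which reproduces section 2.3. This is a pilot rule of thumb with no power formula behind it.

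**2. What the named model uses.** With two visits, the time-by-group test in a mixed ANOVA is the same as a one-way ANOVA on change = post − pre. A participant without a post-test has no change score and drops out of the contrast. This is a property of the method; the article does not state it.

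**3. How many could be lost with retention still a success.** More than 80% of 72 means at least 58 (58/72 = 80.6%; 57/72 = 79.2%). So up to 72 − 58 = 14 can be lost, or 14/72 = 19.4%.
- If all 14 also lack a post-test, 58/3 = about 19 per arm are analysed.
- If all 14 come from the two HIIT arms, (48 − 14)/2 = 17 per HIIT arm are analysed.

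The 10% missing-data expectation has no stated denominator. Counted per participant it allows at most 7 (7/72 = 9.7%). Counted over pre and post records, 14/144 = 9.7% also passes. The worst case of 14 is therefore possible but not established.

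**4. Precision.** The 95% half-width for a pairwise contrast, in SD units of the analysed variable, is 1.96 × √(2/n).
- n = 24: 0.57
- n = 19: 0.64
- n = 17: 0.67

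**5. What baseline adjustment gains.** Assume a pre–post correlation r = 0.7 (not in the article), unit SD and 24 per arm with no loss.
- Change score: SE = √(2(1 − r) × 2/24) = √(0.6 × 2/24) = 0.224 SD.
- Baseline-adjusted: SE = √((1 − r²) × 2/24) = √(0.51 × 2/24) = 0.206 SD, before the small cost of estimating the slope.

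Simulation gives 0.222 and 0.209. The variance ratio is (0.209/0.222)² = 0.89, so adjustment lowers the variance by about 11%.

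**6. Bias under three dropout patterns.** This is an illustrative simulation of one HIIT arm against control: 24 per arm, r = 0.7, no true effect, about 21–25% lost from the HIIT arm and 5% from control, 5,000 replicates per setting. All of these inputs are assumptions.

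| Who leaves the HIIT arm | Change-score contrast (mixed ANOVA) | Baseline-adjusted, same cases |
|---|---|---|
| At random | 0.00 SD | 0.00 SD |
| Depends on baseline | −0.04 to −0.06 SD | about 0.00 SD |
| Poor responders | +0.08 to +0.17 SD | +0.07 to +0.14 SD |

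Baseline adjustment removes the second kind of bias and leaves most of the third.

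**The case against.** The strongest reply has four parts.

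*A fuller plan may settle it.* Analysis sets and imputation methods are commonly left to a statistical analysis plan, which is not shown, and a mixed ANOVA run on imputed data would be compatible with intention-to-treat. This stands as far as it goes: the undefined qualifier or the absent imputation method alone would only be missing detail. What remains is printed text. Intention-to-treat is described as a remedy for missing data, beside a named model that uses only complete pairs.

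*A reader might infer that the plan delivers a completer analysis.* The article does not support that. It states no per-protocol set and no exclusion for poor adherence; section 2.9.1 treats adherence as a feasibility outcome. A student who stops training but attends the post-test stays in the ANOVA. The default is complete-case, not completer. For the same reason 14 is an upper bound, because the retention threshold concerns finishing the intervention, not attending the post-test.

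*A reader might infer that the effect is overstated.* For example, if 20% of a HIIT arm leave with no gain and the rest gain 0.5 SD, the all-randomised effect is 0.8 × 0.5 = 0.40 SD and the complete-case estimate is 25% too high. Both inputs are invented, and the simulation above gives zero or negative bias under other patterns. Nor can that example justify the change of main model: in this scenario a baseline-adjusted analysis of the observed cases also returns 0.50.

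*The stakes are limited.* The primary outcomes are feasibility rates, which this does not touch. The fitness effects are exploratory, and the half-width at 24 per arm is already 0.57 SD. This stands and limits the weight of the point. It does not remove it, since section 2.12 chooses to emphasise these estimates and to size the next trial on them.

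**Conclusion.** The point holds in a limited form. As written, section 2.12 makes analysis as randomised conditional, credits it with handling missing data, and pairs it with a model that is complete-case by default. In the worst case, 14 of 72 participants (19.4%) drop out of the effect estimates while retention still counts as a success.

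This rests on reading the ANOVA as the classical routine, which the sphericity wording supports, and on every non-completer also missing the post-test, which is an assumption. The size and sign of any bias depend on who leaves and cannot be fixed from the article. A baseline-adjusted model is the better main analysis because it is more precise and removes bias from baseline-dependent dropout. It does not cure bias from the loss of poor responders. The change is worth making for the exploratory fitness outcomes; the primary feasibility outcomes are unaffected.

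**What to change.** In section 2.12:

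- Delete 'where appropriate' and state that all randomised participants are analysed in their allocated arm. Stop describing intention-to-treat as the method for missing data.
- Replace the mixed ANOVA as main analysis with a baseline-adjusted model in the software already named: SPSS MIXED by REML with both visits as outcomes and a common baseline mean across arms, or the equivalent ANCOVA of the post-test on baseline and arm. The MIXED version keeps participants with a baseline only. They add little to the contrast; the gain comes from the adjustment.
- Add one sensitivity analysis that assumes no change from baseline for participants without a post-test, because the main model does not protect against the loss of poor responders. It shows how far the result depends on that loss; it is not a correction.
- Keep the complete-case mixed ANOVA as supplementary.

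The cost is revised wording and slightly more analysis work. No visit, measurement or participant is added.

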## 3. Discussion

This study presents the protocol for a mixed-methods feasibility randomized controlled trial designed to evaluate the feasibility and preliminary effectiveness of a time-specific high-intensity interval training (HIIT) programme for improving health-related physical fitness among Chinese college students. By combining quantitative assessments of physical fitness with qualitative exploration of participant experiences, the study aims to provide a comprehensive evaluation of both the practical implementation and perceived acceptability of the intervention in a university setting.

Physical inactivity among college students has become an increasing public health concern globally. Several studies have reported that college students often experience reduced physical activity levels due to academic workload, sedentary learning environments, and competing time demands [34]. Insufficient physical activity during this life stage may have long-term implications for cardiovascular health, metabolic function, and overall well-being [35]. Consequently, developing efficient and accessible exercise interventions that can be realistically integrated into students’ daily schedules is an important priority for public health and university health promotion initiatives.

High-intensity interval training (HIIT) has gained considerable attention as a time-efficient exercise strategy capable of producing meaningful improvements in cardiorespiratory fitness and metabolic health within relatively short training durations [8]. Compared with traditional continuous aerobic training, HIIT requires substantially less time commitment while still eliciting significant physiological adaptations. This makes HIIT particularly attractive for university students who frequently report lack of time as a major barrier to exercise participation. Previous studies have demonstrated that brief HIIT interventions can significantly improve cardiorespiratory fitness, body composition, and metabolic markers in young adults [36,37], further supporting the potential value of HIIT-based programmes for this population.

Another important feature of the present study is the investigation of exercise timing, an emerging topic within exercise physiology and chronobiology. Human physiological processes are regulated by endogenous circadian rhythms that influence hormonal secretion, metabolism, sleep–wake patterns, and physical performance [9]. Growing evidence suggests that the timing of exercise relative to these circadian rhythms may influence both acute physiological responses and long-term training adaptations [10]. This concept, often referred to as chrono-exercise, proposes that aligning exercise timing with circadian biological rhythms may optimize exercise outcomes and potentially enhance adherence to physical activity programmes [13].

Individual differences in circadian rhythm are commonly described through the concept of chronotype, which reflects a person’s natural preference for earlier or later timing of daily activities. Chronotype has been shown to influence exercise performance, motivation, and behavioural responses to physical activity [11]. For example, individuals with morning chronotypes often demonstrate higher physical performance earlier in the day, whereas evening chronotypes may perform better later in the day. Understanding how exercise timing interacts with circadian biology may therefore help optimize training effectiveness and improve adherence to structured exercise programmes [12].

Despite increasing interest in chrono-exercise, empirical research examining the feasibility of time-specific exercise interventions in real-world university settings remains limited. Many previous studies investigating exercise timing have been conducted in controlled laboratory environments or among trained athletes, which may limit their applicability to broader populations such as university students. Therefore, the present study addresses an important gap in the literature by examining whether implementing a structured HIIT programme at different times of day is feasible and acceptable within a university context.

Another strength of the present study is the mixed-methods design, which integrates quantitative and qualitative approaches to evaluate the intervention. While quantitative assessments will provide objective evidence regarding changes in health-related physical fitness indicators, the qualitative interviews will allow participants to describe their experiences with the intervention in greater depth. Understanding participants’ perspectives, including perceived benefits, barriers, and motivational factors, is essential for refining exercise interventions and improving their long-term sustainability. Mixed-methods approaches have increasingly been recommended in feasibility studies because they provide richer insights into intervention implementation and contextual factors influencing participant engagement [14].

The findings of this feasibility trial are expected to contribute to several important areas of research. First, the study will provide evidence regarding the practical implementation of short-duration HIIT programmes within university settings, including recruitment feasibility, participant adherence, and intervention acceptability. Second, the study will generate preliminary data on whether the timing of exercise sessions may influence training responses among university students. Such findings may help inform the design of future chrono-exercise interventions and support the development of more individualized physical activity recommendations.

Nevertheless, several limitations should be acknowledged. The present study only includes participants with an intermediate chronotype in order to reduce circadian variability and improve internal consistency during this preliminary feasibility trial. However, this approach may limit the generalizability of the findings to individuals with extreme morning or evening chronotypes. Therefore, the study does not allow examination of potential chronotype and exercise timing interactions. And the sample size is relatively small; the study may not be powered to detect definitive intervention effects. The study will also be conducted at a single university, which may limit the generalizability of the findings to other student populations or cultural contexts. Because the intervention targets students with low prior physical activity levels, systematic monitoring of adverse events and safety indicators will provide important information on whether short-duration HIIT can be implemented safely and acceptably in this population before proceeding to a larger definitive trial.

Additionally, the intervention duration of eight weeks may not capture long-term behavioural changes or sustained improvements in health-related physical fitness. Future studies may therefore consider multi-site trials, larger sample sizes, and longer intervention periods to further evaluate the effectiveness of time-specific exercise interventions. And future large scale randomized controlled trials should consider including multiple chronotype categories and examining chronotype as a moderating variable influencing exercise adherence and physiological adaptation to time-specific HIIT interventions.

Future research could also expand the scope of investigation by examining additional outcomes such as sleep quality, psychological well-being, and metabolic biomarkers, which are closely linked to circadian physiology and physical activity behaviour. Furthermore, integrating wearable technology and digital health monitoring may provide valuable insights into real-world exercise behaviour and adherence patterns among university students [38].

In summary, this study aims to provide preliminary evidence regarding the feasibility and potential effectiveness of a time-specific HIIT intervention among Chinese college students. The findings are expected to inform the development of future large-scale randomized controlled trials and contribute to the growing field of chrono-exercise research, ultimately supporting the design of more effective and sustainable physical activity interventions for young adult populations.

## 4. Conclusions

This protocol describes a mixed-methods feasibility randomized controlled trial designed to examine the feasibility and potential effectiveness of a HIIT module for improving health-related physical fitness among Chinese college students. The study will also explore the influence of exercise timing and participants’ experiences with the intervention. The findings will provide preliminary evidence to inform the design of future large-scale trials and support the development of practical and time-efficient physical activity interventions in university settings.

## Figures and Tables

**Figure 1 healthcare-14-01443-f001:**
[figure not shown]
Conceptual framework of the time-specific high-intensity interval training (HIIT) intervention.

**Figure 2 healthcare-14-01443-f002:**
[figure not shown]
CONSORT Flow Diagram for the Chrono-HIIT Study.

**Table 1 healthcare-14-01443-t001:** SPIRIT (Standard Protocol Items: Recommendations for Interventional Trials) schedule of enrolment, interventions, and assessment.

Timepoint	Study Period										
	Enrolment	Allocation	Post-Allocation								Close-Out
	2/2026–3/2026	2/2026–3/2026	Week 1	Week 2	Week 3	Week 4	Week 5	Week 6	Week 7	Week 8	5/2026
Enrolment											
Screening	√										
Eligibility	√										
Informed consent	√										
Allocation		√									
Intervention morning group			√	√	√	√	√	√	√	√	
Intervention evening group			√	√	√	√	√	√	√	√	
Control group			√	√	√	√	√	√	√	√	
Assessments											√
Health-related physical fitness		√								√	

**Table 2 healthcare-14-01443-t002:** Detail protocol.

Time	Movements
0:00–0:40	High Knees
0:40–1:00	Rest
1:00–1:40	Jumping lunges
1:40–2:00	Rest
2:00–2:40	Jumping Jacks
2:40–3:00	Rest
3:00–3:40	Bodyweight Squats
3:40–4:00	Rest
4:00–4:40	Burpees
4:40–5:00	Rest
5:00–5:40	Butt kicks
5:40–6:00	Rest
6:00–6:40	Push ups
6:40–7:00	Rest
7:00–7:40	Mountain Climbers
7:40–8:00	Rest

**Table 3 healthcare-14-01443-t003:** Interview guide.

No.	Interview Question
1.	Please describe your experience participating in the HIIT course.
2.	What was the most memorable movement for you throughout the entire module? Why?
3.	During the training, what specific physical changes did you notice? (e.g., fatigue level, heart rate, amount of sweating, muscle sensation)
4.	What impact do you think the HIIT has had on your physical fitness, endurance, or overall physical condition?
5.	How did you typically feel emotionally after participating in HIIT? (e.g., excited, stressed, focused, bored).
6.	During or after the training, did you experience any changes in your sense of accomplishment, motivation, self-confidence, or willpower? Please describe specifically
7.	Were there moments when you felt anxious, apprehensive, or wanted to give up? How did you cope with them?
8.	Do you think the current structure, duration, intensity, and movement arrangement of the HIIT module are reasonable? Why?
9.	What do you think are the advantages and potential disadvantages of this training method, respectively?
10.	Regarding safety, what areas do you think require special attention or need more guidance?
11.	Do you have any suggestions?

